## Abstract

**Background:**

Eating habits are established during childhood and track into adolescence and later in life. Given that these habits have a large public health impact and influence the increasing rates of childhood obesity worldwide, there is a need for effective, evidence-based prevention trials promoting healthy eating habits in the first 2 years of life.

The aim of this study was to develop and evaluate the effect of an eHealth intervention called Food4toddlers, aiming to promote healthy dietary habits in toddlers by targeting parents’ awareness of their child’s food environment (i.e., how food is provided or presented) and eating environment (e.g., feeding practices and social interaction). This paper describes the rationale, development, and evaluation design of this project.

**Methods/design:**

We developed a 6-month eHealth intervention, with the extensive user involvement of health care nurses and parents of toddlers. This intervention is in line with the social cognitive theory, targeting the interwoven relationship between the person, behavior, and environment, with an emphasis on environmental factors. The intervention website includes recipes, information, activities, and collaboration opportunities. The Food4toddlers website can be used as a mobile application. To evaluate the intervention, a two-armed pre–post-follow-up randomized controlled trial is presently being conducted in Norway. Parents of toddlers (*n* = 404) were recruited via social media (Facebook) and 298 provided baseline data of their toddlers at age 12 months. After baseline measurements, participants were randomly allocated to an intervention group or control group. Primary outcomes are the child’s diet quality and food variety. All participants will be followed up at age 18 months, 2 years, and 4 years.

**Discussion:**

The results of this trial will provide evidence to increase knowledge about the effectiveness of an eHealth intervention targeting parents and their toddler’s dietary habits.

**Trial registration:**

ISRCTN92980420. Registered 13 September 2017. Retrospectively registered.

## Background

It is acknowledged that long-term health has an early developmental origin [1, 2]. The period from conception until 2 years of age, “the first 1000 days of life”, is recognized as a critical period for growth and development as the developing child adapts both metabolically and behaviorally to its nutritional and overall environment via gene expression and epigenetic mechanisms [3, 4]. Given that an unhealthy diet is one of the key risk factors for overweight, obesity, and other related noncommunicable diseases (NCDs) [5], diet quality during these formative years may strongly influence the child’s life-long health trajectory [6].

In Norway, as in other countries, unhealthy dietary patterns characterized by low intake of fruits and vegetables and high intake of non-core foods and beverages, are observed among toddlers [7–11]. In addition, at 12 months of age, about 80% of Norwegian children eat commercial baby food, with the main food intake for more than 15% of children aged 24 months still coming from jarred foods [12, 13]. Furthermore, studies have shown unhealthier dietary patterns in young children from families with lower socioeconomic status (SES) than those with higher SES [14–16]. There is a social gradient in child diet quality disfavoring the long-term health of children with lower SES [16, 17].

Parents are the gatekeepers of foods served during the first years of life and they have a unique role in shaping their child’s dietary behavior [18, 19]. Dietary preferences (likes and dislikes) and food habits established early on reflect to a large extent parental feeding practices, such as the type and variety of foods offered during the first 2 years of the child’s life [18]. Early dietary habits have been shown to track to later in childhood and adulthood [7, 20]. Fostering healthy dietary habits is therefore crucial to long-term health and obesity prevention [20]. Whether healthy or unhealthy dietary preferences are established depends on what, when, and how the child is fed [18]. To promote the internal regulation of energy balance, parents should be responsive to a child’s hunger and satiety cues during meals and feeding [21, 22]. One-year old children are capable of eating foods consumed by the whole family, and the development of self-feeding skills should be encouraged in this period [23].

Parental feeding practices are influenced by nutrition knowledge, family meal practices, and overall food preparation and parenting skills [24]. Non-responsive feeding (i.e., excessively controlled feeding, indulgent feeding, or uninvolved feeding) has been linked to childhood obesity [25]. Campbell and Crawford [26] identified several factors in the family environment to be important for children’s diet, including parental food preferences and beliefs, children’s food exposure, role modeling, media exposure, and child–parent interactions around food. In another study, those authors demonstrated several aspects of the family’s food environment (e.g., TV viewing and shared meals) to be associated with child dietary characteristics that are likely to promote fatness [27].

Lobstein et al. [28] claimed that the food environment is the leading factor driving obesogenic behaviors. The *food environment* refers to factors that directly relate to how food is provided or presented such as its salience, structure, packaging or portion size, and how it is served [29]. The food environment is further divided into *macro-scale* (e.g., food shopping outlets) and *micro-scale* (e.g., home environment). The *eating environment* refers to factors that are independent of foods, such as social interactions around meals, atmosphere, and the time of day that meals are eaten [29]. Roberto and Kawachi [30] found that many of people’s daily eating habits are guided by default options, e.g., large portion sizes in restaurants. According to Roberto and colleagues [31], current food environments exploit our biological, psychological, social, and economic vulnerabilities by making it easier to access and eat unhealthy non-core foods that either increase overall energy intake or replace healthy core foods in the diet. In-store environmental factors (e.g., the placement of healthy foods) influences parents’ choices when shopping [32]. The food industry produces jarred food, squeezable fruit pouches, and baby porridge for children up to the age of 24 months and older that are often packed in colorful, attractive wrappings and marketed as a healthy choice. These high-cost products are often strategically placed in the store. These foods are unnecessary for toddlers and do not meet the child’s need for different texture, flavors, and dietary variety [33]. Addressing awareness of how both the macro- and micro-scale food environments affect choices regarding foods and feeding is important, to help parents make more informed choices.

Although interventions at early ages are decidedly needed, they are scarce [34–37]. Two dietary intervention trials in Australia have addressed the parental role in shaping healthy eating environments for young children [22, 38]. The cluster-randomized INFANT study focused on parenting skills related to diet and physical activity in children aged 3–18 months, and resulted in lower consumption of sweet snacks and less daily television time [39]. The NOURISH trial, a community-based intervention targeting early parental feeding practices in 4- to 16-month old children [22], reported higher use of protective feeding practices conducive to the development of healthy eating patterns and healthy growth in the intervention group compared with the control group [40]. To our knowledge, no studies have applied eHealth approaches targeting diet in young age groups via the parents [34, 35, 41].

Interventions using smartphones and computers have a high potential to reach a large number of people, including those with low SES. Such interventions are cost-effective, flexible, have a low participant burden, and may be more visually appealing and engaging [42]. Therefore, we developed an eHealth intervention called Food4toddlers, with a mobile application (app) version for use with a smartphone.

## Objectives and outcomes

The aim of this study was to develop and evaluate the effect of an eHealth intervention called Food4toddlers, aiming to promote healthy dietary habits in toddlers by targeting parents’ awareness of their child’s food and eating environments.

### Primary outcomes

Primary outcomes of the study are child diet quality and food variety assessed at baseline and after the intervention.

### Secondary outcomes

Secondary outcomes include the food and eating environments conceptualized as: parental feeding practices, family meal settings (frequency of meals, meal distractions), food choice, awareness of the food environment (at home and in the grocery store), availability and accessibility of food at home, food preparation and planning, and child weight and length.

## Methods/design

### Study design

This study is a randomized controlled trial to evaluate the effect of the Food4toddlers intervention, in which the intervention group has access to the Food4toddlers intervention website and the control group does not, see Fig. 1. Children in the intervention and control groups receive their usual care at community child health centers, which normally includes three consultations with a health care nurse for children between 12 and 18 months of age. The study started in August 2017 and is ongoing.

**Fig. 1 Fig1:**
[figure not shown]
Flow chart of the Food4toddlers study design

Participating parents complete questionnaires at baseline, post-intervention (end of intervention, after 6 months), and at two follow-ups (i.e., when their child turns 2 and 4 years old). The intervention runs in waves, and the first group started the intervention in September 2017. New groups were started every month through February 2018.

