### Study sample and recruitment

The study population comprised children close to 12 months and one of their parents. To be included in the study, parents had to have a child born between August 2016 and April 2017 and the parents had to be literate in Norwegian. Participants were recruited via Facebook. A short video was launched on Facebook with a link to the project website containing information about the project and the opportunity to sign up. The recruitment period lasted 5.5 months from mid-August 2017 to January 2018. In total 404 parents were recruited. The month before the child reached age 12 months, the enrolled parent received an e-mail with a link to a questionnaire. Three reminders on e-mail were sent to non-responders the following weeks. We included a total of 298 parents who responded to more than half of the survey questions. After they had completed the baseline questionnaire, participants were randomized according to an SPSS-generated randomization list prepared of [name], of 500 to the intervention and control group (SPSS version 24.0). The first author was the one who enrolled participants and assigned participants to the intervention group and control group. Among the participants who answered baseline and post intervention questionnaires, ten participants were selected to receive a gift card of 1000 Norwegian kroners. Demographic characteristics of the sample are provided in Table 1.

**Table 1 Tab1:** Characteristics of participating parents and children

		Intervention (*n* = 148)	Control (*n* = 150)
Parents (*N* = 298)	Mother/father/other (n)	144/4/0	148/0/2
	Age (year), mean (SD))	31.5 (4.4)^a^	31.9 (4.0)
	Height, mean kg (SD)	168.7 (6.0)	168.1 (5.9)^b^
	Weight, mean cm (SD)	70.8 (14.3)	71.1 (14.8)^b^
	BMI, mean (SD)	24.9 (4.6)	25.1 (4.8)^b^
	Two adult household (%)	98.0	96.7
	Family members (n), mean (SD)	3.60 (1.0)	3.65 (0.87)
	Born in Norway (%)	89.2	83.2^a^
Education		^a^	^a^
	Upper-level secondary school or less (%)	12.2	11.4
	College/university (≤4 years) (%)	31.3	36.9
	College/university (> 4 years) (%)	56.5	51.7
Geographic residence			
	Northern Norway (%)	4.5	6.7
	Central Norway (%)	10.8	10.7
	Western Norway (%)	23.0	20.7
	Southern Norway (%)	16.2	20.0
	Eastern Norway (including Oslo) (%)	44.6	42.0
Child			
	Age (months (SD))	10.9 (1.3)	10.8 (1.2)
	Girls (%)	46.6	43.3

^a^one missing, ^b^two missing

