### Website development

A prototype website was developed, and pilot tested with 14 participants in February 2017. The content of Food4toddlers was further refined based on this pilot test, recommendations from health authorities, and updated research in the field.

The website was developed using NEO Learning Management System. Two Masters students in Multimedia and Educational Technology at the University of Agder created a technical layout of the website, and the project group produced the content. The information provided on the website all relates to creating healthy food and eating environments for toddlers.

The homepage of the website contains an informational video about the website and information on why small changes in diet during the early years of a child’s life may be important in the long term. This page also gives some practical information on how to navigate the website and how to use the same information on a smartphone app. There is no difference in usability between the website and the smartphone app.

The website comprises four main elements: modules covering an introduction and seven topics on promoting healthy food and eating environments for the child, recipes, a discussion forum, and general information about food and beverages (the “Good to know” section), as shown in Table 2. When participants first accessed the website, not all content of the modules was visible to them, only the first two chapters. During the intervention period, access was expanded regularly (20 times) to include new content on the website; at this time, all the participants in the same wave received an e-mail with a link to the newly available information.

**Table 2 Tab2:** Content of the intervention

Title	Explanation	Concept development

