### Discussion forum on the website

It was possible for participants to post questions and share information (e.g., recipes) with each other on a discussion forum. A project worker answered questions, usually within 3 working days. Participants who joined the same group had access to the same forum.

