### Statistical analysis plan

For this protocol paper we present descriptive statistics of sample characteristics. All analyses were performed by using IBM SPSS Statistics 25.0.

Intervention effects on child diet, will be examined by use of mixed models (Linear Mixed Models and Generalized linear mixed models) with time as within factor (differences between baseline and post-test, follow-up 1, 2 and 3, respectively) and condition (intervention group, control group) as between-group factor. All models of pre-post outcomes will be adjusted for baseline values to account for regression to the mean effects. Using mixed models allows for use of incomplete data at the different follow-ups and thereby increase statistical power. We will present both crude and adjusted results. Intervention effects on both primary and secondary outcomes will be adjusted for the following variables: parental SES, BMI and age, and child gender and age (variables known from previous research to potentially confound such associations). To examine potential moderating effects such as parental SES (lower versus higher education level), a three-way interaction effect (time*condition*moderator) will be investigated for each outcome. As loss to follow up is expected, loss to follow-up-analyses will be performed, analyzing those lost to follow up compared to those remaining in the study. This will be done to identify if there are characteristics specific of those lost to follow up important to interpret the results.

The data will be stored securely on a password-protected computer with no connection between the data and personally identifiable information. The data will be available after project completion.

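### The intervention is delivered in six monthly groups with a shared forum, but the analysis treats intervention parents as independent; a sensitivity analysis for clustering in that arm is missing

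*Protocol article*

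**What the plan says.** All of this is in the protocol article.

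- **Groups (Study design, text after Fig. 1).** "The intervention runs in waves, and the first group started the intervention in September 2017", and "New groups were started every month through February 2018". September 2017 to February 2018 is six monthly starts.
- **Shared release schedule (Website development).** Content was opened in 20 steps, and at each step "all the participants in the same wave received an e-mail with a link to the newly available information".
- **Shared forum (Discussion forum on the website).** "Participants who joined the same group had access to the same forum". Table 2 describes parents discussing questions and exchanging recipes there. I read group and wave as the same unit.
- **Control arm (Study design).** "the intervention group has access to the Food4toddlers intervention website and the control group does not".
- **Allocation (Study sample and recruitment).** "After they had completed the baseline questionnaire, participants were randomized according to an SPSS-generated randomization list". Individuals are randomised, and no stratification by wave is stated.
- **Model (Statistical analysis plan).** Mixed models with time as the within factor and "condition (intervention group, control group) as between-group factor", adjusted for baseline values and for "parental SES, BMI and age, and child gender and age". Wave is in neither list.
- **Sample size (Study sample and recruitment).** 142 per group, raised to 237 for 40% loss, with no allowance for clustering.

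**The concern.** Individual randomisation makes the two arms comparable, but it does not keep outcomes independent once one arm is treated in groups. Parents who use the same forum can influence one another's feeding choices, and one group's forum may be livelier or better answered than another's. Controls have no counterpart to this, so the design is partially nested, with clustering possible in the intervention arm only.

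An analysis that ignores positive correlation within those groups understates the variance of the intervention-arm mean. The confidence interval is then too narrow and the test rejects too often. At stake is whether a borderline positive result on diet quality or food variety could be defended against the objection that members of six forum groups were counted as independent parents.

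**Working it through.** **1. The plan's own figure.** Difference 3, SD 9.0, power 80%, two-sided 5%: n = 2 × (1.960 + 0.842)² × 9² / 3² = 141.3, so 142 per group. Then 142 / (1 − 0.40) = 236.7, so 237. Both figures reproduce with a design effect of 1, meaning no clustering was allowed for.

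**2. Inputs.** From Table 1: 148 intervention and 150 control. After 40% loss: 148 × 0.6 ≈ 89 and 150 × 0.6 = 90. Number of groups: six, counted from the text. Assumed, because the documents do not say: equal group sizes, and a within-group ICC from 0 to 0.05 in the intervention arm. The ICC is that of the outcome after the planned adjustments.

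**3. Formulas.**
- Intervention-arm design effect: DE = 1 + (m − 1) × ICC, with m = 148/6 = 24.7 or 89/6 = 14.8. The control-arm design effect is 1.
- Ratio of true to planned standard error: r = √[(DE/n₁ + 1/n₂) / (1/n₁ + 1/n₂)]. The outcome SD cancels.
- True two-sided error of a nominal 5% test: 2 × [1 − Φ(1.96/r)].

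Example, ICC 0.05 with everyone retained: DE = 1 + 23.7 × 0.05 = 2.18; r = √[(2.18/148 + 1/150) / (1/148 + 1/150)] = 1.263; 1.96/1.263 = 1.55; error 12.1%.

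| ICC | DE, 148/150 | r | True error | DE, 89/90 | r | True error |
|---|---|---|---|---|---|---|
| 0 | 1.00 | 1.000 | 5.0% | 1.00 | 1.000 | 5.0% |
| 0.01 | 1.24 | 1.058 | 6.4% | 1.14 | 1.034 | 5.8% |
| 0.02 | 1.47 | 1.113 | 7.8% | 1.28 | 1.067 | 6.6% |
| 0.05 | 2.18 | 1.263 | 12.1% | 1.69 | 1.161 | 9.1% |

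**4. Simulation of the formula.** Null data with clustering in the intervention arm only, 148/150 in six waves, 10,000 runs: the unadjusted test rejected in 6.5% of runs at ICC 0.01 and 12.3% at 0.05, in line with the table.

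**5. Does a wave term common to both arms help?** Six equal waves, 150 per arm, 20,000 runs, ICC 0.01 / 0.02 / 0.05. The planned test rejects in 6.7% / 7.6% / 12.3%. With a fixed wave effect common to both arms it rejects in 6.6% / 7.5% / 12.3%, which is no improvement. A wave variance in the intervention arm only, with small-sample degrees of freedom, holds the error at or below 5%. Its price is power: at ICC 0 it falls from 83% to 76%.

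**6. Does shared calendar time matter for validity?** With a wave effect common to both arms and individuals randomised (10,000 runs), the unadjusted test rejected in 4.8% of runs at ICC 0.01 and 5.2% at 0.05. Simulation error is about 0.2 percentage points, so both are nominal.

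**The case against.** The strongest reply is that the correlation may be negligible. Most of the programme is a website used individually. The forum is one of four elements, posting is optional, and a project worker answers questions. The release e-mails deliver the same programme to every wave, so a common schedule does not by itself make group means differ. No ICC or forum use is reported, and zero fits the documents as well as 0.05 does. All of this stands. It is why the range starts at zero and why no change to the primary model is asked for.

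A second reply is that the article condenses a fuller plan, and that random terms and sensitivity analyses often sit there. This also stands in part: the article does not spell out its random-effects structure. But it does give an explicit list of factors and covariates, and that list omits a delivery feature described in three separate sections. That makes the point worth raising, at modest weight.

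Three stronger readings are tempting, and the documents do not support them.

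- A reader might infer that leaving out calendar month also makes the standard errors wrong. It does not: individuals are randomised to concurrent arms, so seasonal variation common to both only adds residual noise.
- A reader might infer that Table 1's child-age SD of 1.2 to 1.3 months shows how much age varies within a wave. Those SDs are per arm, pooled over all waves.
- A reader might assume that every control belongs to a wave. The article describes waves only for groups starting the intervention.

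**Conclusion.** The point holds conditionally. The partially nested structure is documented, and the listed model does not account for it. Whether the error rate is actually inflated depends on an ICC that the documents do not give. Over the assumed range of 0 to 0.05, a nominal 5% test has a true error between 5% and about 12% with all 298 participants, and between 5% and about 9% after 40% loss. Unequal group sizes would change these figures, and the equal-group assumption is mine.

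It would go too far to say that the planned test is shown to exceed 5%, or that the primary analysis has to be replaced. The evidence supports one prespecified check on how robust the primary result is to clustering in the intervention arm.

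**What to change.** Keep the planned model as primary. Add to the Statistical analysis plan section one prespecified sensitivity analysis of the two primary outcomes, child diet quality and food variety. It should have a random group effect in the intervention arm only, each control treated as a group of one, and small-sample degrees of freedom. Report its confidence interval beside the primary one.

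The cost is analysis-plan wording and one additional model per primary outcome. The downside is that a variance estimated from six groups is imprecise and the interval will be wider. The power loss shown in step 5 is why this belongs in a sensitivity analysis.

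Start or baseline month as a fixed covariate is optional. It can gain only a little precision, it does not correct the clustering, and for controls it would have to be derived from the baseline date.
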